### Methods of Analysis

#### Descriptive Statistics: Baseline Characteristics

The baseline demographics and clinical characteristics of general practices and individual participants will be reported. The CONSORT guidelines generally do not recommend statistical significance testing of baseline imbalances between trial arms. However, a more recent publication suggests baseline testing of individual-level characteristics for cluster RCTs to examine the level of selection bias as indicated by potential imbalances in baseline covariates between arms [63].

#### Main Analysis of Primary Outcomes

To avoid any potential bias in the analysis, intention to treat (ITT) will be the primary analysis population (including primary and secondary outcomes) unless otherwise stated in the detailed statistical analysis plan (available from the authors). This is defined as general practice clusters (and affiliated participants) being analyzed as they are randomized regardless of the intervention. Data for individuals who withdraw consent to participate in data collection will be included up to the point of withdrawal. Primary analysis will compare mean differences in pain intensity scores between trial arms over a 6-month follow-up using a hierarchical linear mixed regression model evaluating repeated measures data at 1-, 2-, 3-, 4-, 5-, and 6-month follow-up (level 1) within individuals (level 2) and taking into account clustering of individuals within general practices—the unit of randomization (level 3). The analyses will be adjusted for age, sex, and baseline pain intensity score (recorded from the IT template at the point of consultation) at the individual-patient level and general practice size. This analysis fulfills the ITT principle with analysis as randomized and missing data being accounted for under the missing at random assumption. Although the primary analysis will focus on the *average* intervention effect across 1 to 6 months of follow-up, we will also use treatment by time interaction terms to evaluate between-arm differences in mean responses across each of the individual time points of 1, 2, 3, 4, 5, and 6 months. Model fit will be assessed across different covariance structures (unstructured, independence, exchangeable, autoregressive) to ascertain the best-fit model that will be implemented (ie, the model that gives the lowest Bayesian Information Criterion, Akaike Information Criterion, and highest log-likelihood statistics). The monthly pain intensity scores will be used; however, if, for any individual, the last monthly SMS/brief questionnaire response is missing but they have completed the corresponding pain intensity question in their returned 6-month questionnaire (if completed within 20 days of the date of issue of their monthly SMS/brief questionnaire), then the available pain intensity score response will be used (as the 6-month score) for purposes of the primary outcome evaluation.

#### Analysis of Secondary Outcomes

Analysis of secondary outcomes will be carried out using the ITT approach and using a linear mixed model for numerical outcomes and generalized mixed logistic models for categorical outcomes (adjusted for age, sex, baseline pain, and corresponding baseline score [where applicable] at the individual-patient level and general practice size). For monthly follow-up measures of distress and confidence in managing pain, the analysis will follow that of the primary analysis with initial focus on *average* scores over the 6 months of follow-up and then the time-specific between-arm estimates. The focus of the other secondary measures is on 6-month follow-up data only, with the exception of perceived reassurance, which is captured in the baseline questionnaire.

#### Sensitivity Analysis of the Primary Outcome

A sensitivity analysis will be carried out using a complier average causal effect analysis (CACE) to provide an unbiased estimate of intervention effect for patients treated according to the stratified care protocol, that is, the intervention arm *protocol* is taken as clinical management in line with the recommended matched treatment options for each risk subgroup. CACE will be performed using a 2-step instrumental variable regression modeling approach where the first step relates to model prediction of *compliance* (at level 2 [individual patient level]) using trial arm only as a fixed-effect predictor and practice and participant IDs as random effects, and the second step estimates the between-arm difference in outcome (*average* pain intensity) based on predicted compliance—the endogenous (instrumented) variable (from the first step) and the exogenous (instrumental) variables of trial arm, age, sex and point-of-consultation pain score using a mixed effects model as used in the primary analysis.

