## Methods

### Study Design and Setting

The Start MSK trial is a pragmatic, two-arm, parallel, cluster randomized controlled trial (RCT), with a linked health economic analysis and mixed methods process evaluation. The setting is UK primary care, and the trial will include approximately 24 average-sized general practices with a total registered adult population of approximately 120,000. General practices will be randomized to either the stratified care intervention (12 practices) or the usual, nonstratified care (12 practices). The units of randomization are the general practices, and the units of observation are adults consulting for MSK pain with 1 of the 5 most common MSK pain presentations (Figure 1).

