### Sample Size

In an average-sized UK general practice (6000 registered adults), we expect that about 800 potentially eligible patients will consult with the MSK pain sites of interest per year or 400 over 6 months. The feasibility and pilot trial showed that, on average, the template was activated 375 times over 6 months in each practice, and clinicians fully completed it in 41.1% (154/375) of cases (6 times per week), leading to a letter inviting the patient to participate in the data collection. From this, we expect that 40% of patients invited will return their initial questionnaire in the main trial, be eligible, and consent to further data collection (or 62 over 6 months in 1 practice). However, to be more cautious, given the general uncertainty in data and in generalizability of pilot estimates, we have conservatively estimated the average number of participants recruited per practice within 6 months in the main trial to be around 33% of those invited (or n=50 in 6 months or n=9 per month per practice).

The trial is powered at 90% to test the hypothesis of the overall superiority of stratified primary care versus usual care based on an alpha of 5% (two-tailed) to detect a small *effect size* (standardized mean difference) of 0.2 [54] in the primary outcome (pain intensity). An effect size of 0.2 was considered to be appropriate based on information from the feasibility and pilot trial, in which the proportion of responders in the 3 risk subgroups was 32% at low risk, 55% medium risk, and 13% high risk. Our previous trial of stratified care for patients with low back pain (the Start Back trial) found an effect size of 0.3 and 0.4 in the primary outcome (back pain–related physical function) in patients at medium and high risk, respectively. Therefore, we have assumed these standardized differences in this new trial [19]. In addition, the minimal clinically important difference for the numerical rating scale (NRS) pain intensity scores in MSK pain has been reported to be 1 point [55], which equates to an effect size of about 0.4, relative to an expected SD of about 2.5 [54]. We expect that there would be little or no difference between stratified care and usual care for patients in the low-risk subgroup. Hence, by multiplying these effects by the expected proportion within each subgroup, the overall effect size of interest is 0.2 (equating to an absolute mean difference of approximately 0.5 in pain intensity on a 0-10 scale).

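### As written, step 2 of the CACE analysis enters trial arm beside a compliance prediction built from trial arm, so the complier effect is either not identified or rests on non-randomised differences

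*Protocol article*

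**What the plan says.** In the section Sensitivity Analysis of the Primary Outcome, the article plans a two-step instrumental variable analysis "to provide an unbiased estimate of intervention effect for patients treated according to the stratified care protocol".

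- **Step 1** models patient-level compliance "using trial arm only as a fixed-effect predictor and practice and participant IDs as random effects".
- **Step 2** estimates the between-arm difference in average pain from predicted compliance, labelled the endogenous (instrumented) variable, together with "the exogenous (instrumental) variables of trial arm, age, sex and point-of-consultation pain score using a mixed effects model", of the kind used for the primary analysis.

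The section Main Analysis of Primary Outcomes defines that primary model: monthly scores within individuals within practices, adjusted for age, sex, template pain score and practice size. Under Study Design and Setting, "The units of randomization are the general practices".

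The article does not say that arm is left out of step 2. It also does not say whether predicted compliance is taken from the fixed part of step 1 alone or includes the random effects.

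**The concern.** An instrumental variable estimate needs a variable that shifts compliance, is randomised, and is kept out of the outcome equation. Here that variable can only be trial arm. If arm is also a regressor in step 2, no excluded instrument remains. The coefficient on predicted compliance then has either no information behind it or only information that randomisation does not protect.

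This is the only estimate in the article of the effect in patients managed in line with the matched options. An analyst who follows the sentence literally would report either whatever the software leaves after dropping a collinear term, or an as-treated contrast presented as unbiased.

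**Working it through.** The article gives no figure for the CACE, so there is none to reproduce. The check is algebra, followed by an illustration.

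**1. Prediction from fixed effects only.** Let A be arm (0 or 1), and let c0 and c1 be predicted compliance in control and intervention. With arm as the only fixed predictor,

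P = c0 + (c1 − c0)·A.

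This holds for a linear or a logistic step 1, because P takes one value per arm either way. Put P into step 2 with arm:

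Y = b0 + b1·P + b2·A + covariates = (b0 + b1·c0) + [b1·(c1 − c0) + b2]·A + covariates.

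Only the sum b1·(c1 − c0) + b2 can be estimated, and it equals the intention-to-treat difference. Take the article's target difference of 0.5 points (negative means less pain) and an assumed compliance difference of 0.6. The pairs (b1, b2) = (−0.83, 0), (0, −0.5) and (−2, +0.7) then fit equally well, since each gives 0.6·b1 + b2 = −0.5. Only b2 = 0, that is arm removed, gives the complier effect: −0.5/0.6 = −0.83. Age, sex and pain in step 2 do not help, because P does not depend on them.

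**2. Prediction including random effects.** P now also varies within an arm. With A in step 2, b1 is estimated from that within-arm variation alone. Practices were randomised to arm, not to their level of compliance, so a practice that complies more and has better outcomes for other reasons biases b1. A participant random effect is no safer. With one compliance value per person it is either inseparable from residual error or pulls P towards observed compliance, which is an as-treated comparison.

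**3. Illustration (2,000 simulated trials per scenario).**

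Inputs from the Sample Size section: 24 practices, 50 patients each, SD about 2.5, ICC 0.01 (between-practice outcome variance 0.0625 = 0.01 × 2.5²).

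Assumed inputs, not in the article: complier effect −0.80; 60% compliance in intervention; 0% or 30% in control; between-practice SD of compliance 0.12; a shift of 0, −0.15 or +0.15 points in practice outcome per SD of practice compliance (correlation 0 or ±0.15/0.25 = ±0.6).

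| Practices with higher compliance have | Arm kept, practice-level prediction: median (SD), control 0% / 30% | Arm removed, fixed-part prediction: mean (SD), control 0% / 30% |
|---|---|---|
| better outcomes anyway | −2.36 (6.20) / −2.30 (0.88) | −0.79 (0.27) / −0.77 (0.56) |
| no such link | −1.08 (2.25) / −1.03 (9.65) | −0.80 (0.26) / −0.78 (0.56) |
| worse outcomes anyway | +0.21 (6.41) / +0.23 (0.86) | −0.81 (0.27) / −0.82 (0.57) |

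With the fixed-part prediction and arm kept, the design matrix (intercept, P, A, one covariate) had rank 3 of 4 in every run.

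**4. Cross-check of the medians by hand.** Predicted practice effects are shrunk by k = 50 × 0.0144 / (50 × 0.0144 + 0.2256) = 0.76, where 0.0144 = 0.12² and 0.2256 = 0.6 × 0.4 − 0.0144. The expected coefficient is about −0.80/0.76 = −1.05 plus the confounding term ±0.15/0.12 = ±1.25. That gives −2.30, −1.05 and +0.20, in line with the table.

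**The case against.** The strongest defence is that the sentence lists variables in the style of instrumental variable software. The method is named as such, predicted compliance is labelled instrumented and arm instrumental, and an instrument is by definition excluded from the outcome equation. On that reading the analysis would be sound on identification. The possibility stands, but the sentence does not fit it. Arm, age, sex and pain all receive the same label. If all four were instruments, step 1 could not be restricted to arm. If all four are step 2 covariates, no instrument is left. The text needs correcting on either reading.

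A second defence is that the article condenses a statistical analysis plan that is not shown. That answers a charge of omission, so the lack of a stated standard-error method or prediction type is no finding. It does not answer a model that is stated and does not work.

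A reader might infer more than the article supports:

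- *That leaving age, sex and pain out of step 1 biases the estimate.* Under randomisation it does not do so materially. In 2,000 runs for each of three assumed links between compliance and a prognostic covariate (true effect −0.83, arm removed from step 2), an arm-only step 1 gave means of −0.83, −0.82 and −0.83. Adding the covariate to step 1 gave the same means, and the SDs (0.285 to 0.296) agreed to three decimals.
- *That practice size has been dropped.* The cross-reference to the primary model can be read as bringing it in.
- *That the bias has a known size.* It does not. Zero compliance in control is doubtful in particular: the low-risk options include advice and education, which usual care also offers.

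**Conclusion.** The point holds for the analysis as written. With fixed-part predictions the complier effect is not identified, and this depends on no assumed value. With random-effect predictions it is identified only by non-randomised variation within arms, contrary to the stated aim.

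The simulated medians, from about −2.4 to +0.2 against a true −0.80, show how far and how erratically the estimate can move. They rest on assumed compliance rates, between-practice SD and correlations, and they are not a forecast for this trial. The documents do not establish that the authors intended this model, only that the sentence specifies it.

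The primary intention-to-treat analysis and the sample size are untouched. This should be fixed, but it does not threaten the main result.

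**What to change.** Amend the description of the CACE analysis to say that:

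1. trial arm is the sole excluded instrument and does not enter step 2;
2. predicted compliance comes from the fixed part of step 1 only;
3. step 2 regresses pain on predicted compliance plus the primary-model covariates (age, sex, template pain score, practice size), and these covariates are not called instrumental;
4. the confidence interval allows for both steps and for clustering, for example by a bootstrap that resamples practices and repeats both steps;
5. the estimate is consistent under the instrumental variable assumptions, including the exclusion restriction, in place of the claim that it is unbiased.

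If the unpublished analysis plan already specifies this, a clarifying sentence in the trial report is enough. The cost is wording and a few lines of code, with no new data.

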#### Subgroup Exploratory Analysis of Primary Outcomes

Subgroup exploratory analysis of the primary outcome (*average* pain intensity) will be carried out by modeling intervention arm interaction terms within the regression models for (1) risk subgroups (low [reference category], medium, and high risk), (2) single MSK pain (reference) site versus multisite pain, and (3) pain site (back [reference], shoulder, knee, and neck). Subgroup analysis was performed regardless of the results of the primary analysis. The mean between-arm difference (and 95% CI and *P* value) will be computed for each subgroup comparison and visually displayed via a forest plot. The main focus will be on the *average* pain intensity rather than on 3-way interactions of intervention-subgroup-time, but the 3-way interaction results will also be examined (and descriptive results produced by subgroup).

#### Exploratory Mediation Analyses

If there is a significant between-arm difference in the primary outcome (overall pain intensity), then we will carry out exploratory mediation analysis by structural equation modeling to examine (1) which potential mediators are *causal* in effect. (2) if psychological mediators (psychological distress or pain self-efficacy in months 1-5) are on the causal pathway for effect, and (3) if patient-perceived reassurance mediates direct/indirect associations of 6-month pain intensity outcomes.

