2. Undertaking a process evaluation to explore how stratified care, as a complex intervention, interacts with existing patterns of service organization, professional practice, and professional-patient interaction. The evaluation will use mixed quantitative (eg, a mediation analysis) and qualitative methods, integrating data both at the collection and analysis stages, to generate more detailed and comprehensive findings.

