### Process Evaluation

A process evaluation is planned to explore a range of potential factors that might influence differences between trial arms as well as to better understand how stratified care is used and perceived by patients and clinicians. Following recent Medical Research Council guidance on process evaluations for complex interventions [49], we have designed a mixed methods approach [50]. This will use quantitative analyses focusing on a priori hypothesized intervention targets and qualitative approaches using focus groups and interviews.

A key aim of the process evaluation is to better understand the role of potential intervention targets (mediators) on differences in outcomes between the trial arms [51]. The evidence from our previous stratified care trial (for back pain, the Start Back trial) suggested that the identification and targeting of psychological distress among patients at high risk led to improved outcomes [52]. In addition, a systematic review has recently summarized available evidence and identified pain self-efficacy as another potential mediator [53]. Evidence from the Keele Implementation to Improve Patient Care through Targeted treatment Back study [20], which sought to implement our stratified care approach for patients with low back pain consulting in general practice, suggested that important clinical behavior changes included more systematic identification of patients who are *at risk* of persistent disabling pain who need additional support (leading to more referrals to physiotherapy). After careful consideration by the trial team, a number of potential treatment mediators have been identified a priori, including 3 potential factors at the patient level: (1) reduction in levels of psychological distress measured each month with a single item, (2) increases in pain self-efficacy measured each month with a single item, and (3) the extent of patient-perceived reassurance during the index primary care consultation measured via the initial questionnaire. Changes in these potential patient-level treatment mediators will be examined within a mediation analysis using causal modeling techniques (eg, structural equation modeling) to confirm if they are in the causal pathway explaining any observed between-arm differences in outcome with results also examined at each subgrouping level (low, medium, and high).

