In addition, we have identified a number of a priori potential mediators at the level of clinical behavior, measured using the medical record data, including the proportion of patients who receive prescription medications for MSK pain, referrals to other services (eg, physiotherapy and secondary care specialists), referrals for investigations (eg, radiographs, MRI/Computerized Tomography (CT) scans, blood tests), sick certifications (fit notes), and further MSK-related consultations. We will test if there are significant differences in these behaviors between intervention and control practices and whether any of these differences are associated with the results in terms of patients’ pain intensity.

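### The patient-level mediation analysis is promised without condition and by risk subgroup, but is run only if the overall pain result is significant

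*Protocol article*

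**What the plan says.** Three sections of the protocol article speak to mediation.

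- **Secondary Objectives**, objective 2, sets up a process evaluation: "The evaluation will use mixed quantitative (eg, a mediation analysis) and qualitative methods". Mediation is named only as an example, and no condition is attached.
- **Process Evaluation** goes further: "A key aim of the process evaluation is to better understand the role of potential intervention targets (mediators) on differences in outcomes between the trial" (that is, between its two arms). It lists three patient-level mediators chosen in advance (distress, pain self-efficacy and perceived reassurance) and states: "Changes in these potential patient-level treatment mediators will be examined within a mediation analysis using causal modeling techniques". The stated purpose is "to confirm if they are in the causal pathway explaining any observed between-arm differences in outcome", and results are also to be examined within the low-, medium- and high-risk groups. No significance condition appears.
- **Exploratory Mediation Analyses** adds the condition: "If there is a significant between-arm difference in the primary outcome (overall pain intensity), then we will carry out exploratory mediation analysis". The result that must be significant is overall pain intensity, that is, the average effect in all patients.

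Two neighbouring analyses are treated differently. For clinician behaviours, the Process Evaluation section says "We will test if there are significant differences in these behaviors between intervention and control practices" and adds an examination of their association with pain, with no condition. For the subgroup analysis of pain, the article says "Subgroup analysis was performed regardless of the results of the primary analysis".

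**The concern.** A reader of the Process Evaluation section expects the mediation analysis whatever the trial shows. A reader of the Exploratory Mediation Analyses section expects it only after a significant primary result. Both are commitments in the article itself, so this is not a detail left to the analysis plan.

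The condition also looks at the wrong quantity for part of what is promised. Mediation is planned by risk group, but the condition rests on the average over all risk groups. The Sample Size section expects little or no effect in the low-risk group, which dilutes that average. The Process Evaluation section draws its case for distress as a mediator from high-risk patients, who made up 13% of pilot responders. A significant total effect is not needed for an indirect effect to exist, since paths can offset each other or be confined to one subgroup.

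At stake are the estimates of how the mediators relate to pain and of the indirect effects, overall and by risk group. These would be dropped after a non-significant primary result, even if the subgroup analysis pointed to an effect in medium- or high-risk patients.

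**Working it through.** **Step 1. Reproduce the plan's sample size.** Inputs from the Sample Size section: standardised difference 0.2, two-sided alpha 5%, power 90%, ICC 0.01, coefficient of variation of cluster size 0.65, mean cluster size 50, loss 25%, correlation 0.7 among six repeated measures, correlation 0.5 with baseline.

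- Unadjusted size: 526 per arm (article: 525).
- Inflation: [1 + ((0.65² + 1) × 50 − 1) × 0.01] / 0.75 = 1.701 / 0.75 = 2.27 (article: 2.3).
- Deflation: (1 + 5 × 0.7)/6 − 0.5² = 0.75 − 0.25 = 0.50 (article: 0.5).
- Product: 2.268 × 0.50 = 1.134, so 526 × 1.134 = 597 per arm. With the article's rounded factor, 525 × 1.15 = 604. The article's target is 600.

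The design figures reproduce and can be used for the next step.

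**Step 2. How often does the condition block the analysis?** It does so whenever the primary test is not significant. The effective size is 600 / 1.134 = 529 per arm (522 with the factor 1.15), so SE = √(2/529) = 0.0615 SD. For a true standardised difference δ:

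P(not run) = 1 − [Φ(δ/SE − 1.96) + Φ(−δ/SE − 1.96)]

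| True δ | Source | Mediation not run |
|---|---|---|
| 0.20 | planned effect | about 10% |
| 0.15 | assumed | about 32% |
| 0.10 | assumed | about 63% |
| 0.05 | assumed | about 87% |
| 0 | null | 95% |

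The result is not sensitive to how attrition enters. With the cluster size after loss (50 × 0.75 = 37.5), the inflation is 1.523 / 0.75 = 2.03 and power at δ = 0.10 is about 40%, so the analysis is not run about 60% of the time.

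**Step 3. The subgroup mismatch.** The Sample Size section gives risk-group shares of 32%, 55% and 13% and assumes effects of about 0, 0.3 and 0.4. The weighted average is 0.55 × 0.3 + 0.13 × 0.4 = 0.217, which the article takes as 0.2. Suppose instead, as an illustration only, that the high-risk effect of 0.4 alone were real. The overall effect would be 0.13 × 0.4 = 0.052, δ/SE = 0.85, and the condition would block mediation about 86% of the time, including in the group that had the effect.

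**Step 4. What is and is not conditional.**

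| Analysis | Section | Conditional on the primary result? |
|---|---|---|
| Arm effect on monthly distress and self-efficacy; reassurance also covered | Analysis of Secondary Outcomes | No |
| Clinician behaviours and their association with pain | Process Evaluation | No |
| Complier average causal effect | Sensitivity Analysis of the Primary Outcome | No |
| Effect on pain by risk group | Subgroup Exploratory Analysis | No |
| Process outcomes and fidelity | Evaluation of the Process Outcomes | No |
| Qualitative study | Linked Qualitative Study | No |
| Mediator-to-pain paths and indirect effects | Exploratory Mediation Analyses | Yes |

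**The case against.** The strongest reply is that little is lost. Distress, self-efficacy and reassurance are secondary outcomes in their own right, and the Analysis of Secondary Outcomes section places no condition on them. The clinician-behaviour, compliance, subgroup, fidelity and qualitative work also goes ahead. Restricting exploratory mediation to the case where there is a total effect to decompose is a common and defensible choice that limits searching after a null result. The Process Evaluation section's own purpose clause, "to confirm if they are in the causal pathway explaining any observed between-arm differences in outcome", presupposes a difference to explain, so the later section can be read as making that premise operational. The article hypothesises no opposing paths, and a low-risk group with no effect means dilution, not reversal. Finally, the percentages above are simply one minus power. They show how often the condition applies, not how much is lost.

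Most of this stands, and it rules out stronger readings that a reader might infer:

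- That a null trial could not tell whether the intervention shifted the mediators. The secondary analyses address this directly.
- That the monthly mediator data would go unused. They feed those same analyses.
- That the condition contradicts the secondary objective itself. The objective names mediation only as an example, and the process evaluation proceeds either way.

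The reply does not remove the mismatch between the two sections. An observed difference is not the same as a significant overall one, and the phrase can equally cover a difference within a risk group. Nor does it explain why mediation promised by risk group should depend on the overall mean when the subgroup analysis itself does not.

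**Conclusion.** The point holds in a limited form. The Process Evaluation and Exploratory Mediation Analyses sections disagree on whether the patient-level mediation analysis is conditional, though the purpose clause softens the disagreement. A condition on the overall mean also suits neither the promised risk-group mediation nor the expected pattern of effects.

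The condition would drop the mediator-to-pain paths and indirect effects about 10% of the time at the planned effect, about 63% at half that effect and 95% under no effect. These figures rest on the article's design inputs, full recruitment of 600 per arm and a normal approximation. Only the effect of 0.20 is the article's own; the intermediate values and the high-risk-only scenario are assumptions.

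No primary estimate, error rate or sample-size figure is wrong on this account. This is a worthwhile, cheap improvement to an exploratory analysis and does not threaten the trial's main conclusion.

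**What to change.** Delete the opening condition in the Exploratory Mediation Analyses section. Report the pre-specified arm-to-mediator paths, mediator-to-pain paths and indirect effects whatever the primary result, overall and by risk subgroup, with confidence intervals that allow for clustering by practice. Label them exploratory and state that they will not be used to claim effectiveness.

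If the sponsor prefers to keep the condition, the minimum is to state it in the Process Evaluation section and at objective 2, and to say what then happens to the risk-group mediation. This is the weaker option, because it leaves the subgroup mismatch in place.

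The Results section of the article says that analysis is in progress, so any change should be dated and its timing relative to knowledge of the primary result recorded.

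The cost is a little more analysis work. The mediators are already collected (Table 1: distress and self-efficacy monthly, reassurance in the initial questionnaire), and the primary alpha and sample size are untouched. The downside is that indirect effects reported after a null result need cautious interpretation, particularly in the small high-risk group.
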